### Participant timeline {13}

A schematic diagram of the study is presented in Fig. 2. The total study duration for participants will be up to 3 months. During the 90-day study period, patients will be taking their assigned medication and attending one clinical visit 6 weeks after surgery outside the study protocol. They will undergo two monthly telephone interviews. At the end of the 90-day treatment period, they will be invited for a clinical visit when they will undergo a planned cardiac CT and heart ultrasound.

**Fig. 2 Fig2:**
[figure not shown]
Study schematic diagram. ASA, acetylsalicylic acid; AVR, aortic valve replacement; POD, postoperative day; R, randomization; TD, twice daily

A timeline of enrolment, interventions, and assessments is provided in Fig. 3. Participants will initially be screened upon admission to the Department of Cardiac Surgery at the University Hospital Center Zagreb. During screening, all the study inclusion and exclusion criteria will be analyzed, particularly any potential indication for long-term oral anticoagulation or dual antiplatelet therapy or history of hemorrhagic diathesis. If deemed eligible and after signing the informed consent (Fig. 4), they will be scheduled for randomization on the fifth postoperative day following first time isolated rapid deployment AVR surgery. Prior to hospital discharge patients will undergo a planned hemodynamic evaluation of the newly implanted rapid deployment bioprosthetic aortic valve with echocardiography to confirm the definition of successful AVR. Absence of complications will include stroke, acute myocardial infarction, reoperation for bleeding or any other reason, and clinically significant valve thrombosis prior to hospital discharge.

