### Eligibility criteria {10}

All patients aged 65 or older with severe aortic stenosis and no indication for anticoagulation who will undergo first-time isolated AVR at the University Hospital Center Zagreb will be screened for eligibility to participate in the study. Aortic valve replacement will be performed with new generation rapid deployment bioprosthetic aortic valves. Indications for surgical treatment of aortic valve disease will be based on Heart Team discussions, according to the guidelines and standard medical practice. Screening of subjects for inclusion in the research will be done prior to surgery after the admission to the Department for Cardiac Surgery at the University Hospital Center Zagreb.

Definition of successful AVR will be based on echocardiographic criteria and the absence of complications during hospital stay. These echocardiographic criteria should be met on the postoperative ultrasound of the heart prior to hospital discharge: mean aortic valve gradient < 20 mmHg, the highest transvalvular velocity 3.0 m/s, and absence of mild or greater aortic regurgitation. Absence of complications will include stroke, acute myocardial infarction, reoperation for bleeding or any other reason, and clinically significant valve thrombosis prior to hospital discharge.

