### Criteria for discontinuing or modifying allocated interventions {11b}

Patients randomized to the control arm who develop an indication for anticoagulation (e.g., atrial fibrillation) during follow-up will cross over to the apixaban group. Conversely, patients in the intervention group who develop an indication for antiplatelet therapy (e.g., percutaneous coronary intervention) will cross over to the ASA group. All patients will remain as originally allocated for the intention-to-treat analysis of initial strategy. Per-protocol analysis will be performed for safety composite outcomes.

An investigator may withdraw a participant from the study for the following reasons: (1) significant study intervention non-compliance; (2) identification of a clinical adverse event, laboratory abnormality, or other medical condition which could harm the patient in any way by continued participation in the study; (3) if the participant meets an exclusion criterion that precludes further participation; (4) participant requests withdrawal from the trial.

In case of an overt valve thrombosis, ischemic stroke, or systemic embolism before the end of the study, patients will be managed according to the best standards of care regardless of the study protocol allocation. Additional cardiac imaging including a heart ultrasound (transthoracic and/or transesophageal) and, if necessary, a cardiac CT will be considered. The result of this additional imaging as well as previous imaging exams of the heart will be available to the treating physician for evaluation and decision on the appropriate antithrombotic treatment. If necessary, the study drug will be stopped and anticoagulant therapy with unfractionated heparin and/or a VKA will be introduced. On the other hand, if an overt Valve Academic Research Consortium 3 (VARC-3) Type 2–4 bleeding event [18] occurs, the study drug will be discontinued. In any case, immediate medical care, and treatment, including hospitalization will be available.

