## Assignment of interventions: allocation

### Sequence generation {16a}

We will use the R software to generate a random sequential list of binary codes by participant number. Blocks of fixed length will be applied to keep the number of both arms relatively balanced. Set seed function will be used to ensure that the randomization schedule is reproducible. Participants who have been screened and meet criteria will enter the randomization section and be assigned with the appropriate number and corresponding intervention upon confirmation at the first clinic visit.

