### Implementation {16c}

Trained research assistants will enroll participants. Once a patient has been successfully screened, a binary code that is to be allocated to each participant will be generated. Participants will be assigned to interventions based on whichever binary code they are allocated.

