#### Echocardiography

Echocardiography is a widely accessible and validated method of assessing bioprosthetic valve function. An echocardiographic examination will be performed on two occasions during the study. The first one will be done during the index hospitalization, after AVR prior to discharge. It will assess for the definition of successful aortic valve replacement. The second echocardiographic examination will be done 90 ± 5 days after randomization. Repeated echocardiograms at baseline and at 3 months will determine the degree of hemodynamic valve deterioration as suggested in VARC-3 [18]. All echocardiograms will be blindly adjudicated at a core lab.

Echocardiographic examinations will be based on transthoracic echocardiography (TTE) and guidelines for echocardiographic assessment of prosthetic valves [22]. Transthoracic echocardiography is the gold standard in assessing the hemodynamic characteristics of bioprosthetic heart valves. It follows the same principles as for native heart valves although it has some peculiarities. Two-dimensional TTE will be used as the first line of imaging, and three-dimensional transesophageal echocardiography (TEE) will be performed in cases of bioprosthetic dysfunction. Comprehensive echocardiographic imaging of a prosthetic valve involves the use of multiplanar views with care to confirm appropriate leaflet morphology and motion and to identify the presence of calcifications or structural abnormalities of any component of the prosthesis.

Transthoracic echocardiography Doppler imaging will be performed at an imaging speed of 100 mm/s. The parameters that will be recorded are the bioprosthetic aortic valve mean gradient and the effective orifice area (EOA). Measurements will be performed during two cardiac cycles in sinus rhythm. In the case of atrial fibrillation, Doppler measurements will be performed during the period of physiological heart rate and through five cycles. For EOA calculations, the continuity equation obtained from the stroke volume will be used. It is recommended to adjust the cycle length to 10%. Doppler imaging will be done during quiet breathing or in the middle of expiratory apnea.

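### The inclusion criterion of successful valve replacement is judged up to hospital discharge, although randomisation and first dose are on postoperative day 5, so one event can be both a trial outcome and a failure of eligibility

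*Protocol article*

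**What the plan says.** The Inclusion criteria section of the protocol article admits patients whose first isolated aortic valve replacement was successful. Eligibility criteria {10} gives the meaning: "Definition of successful AVR will be based on echocardiographic criteria and the absence of complications during hospital stay". The complications listed are stroke, acute myocardial infarction, "reoperation for bleeding or any other reason, and clinically significant valve thrombosis prior to hospital discharge".

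Participant timeline {13} says of consenting patients that "they will be scheduled for randomization on the fifth postoperative day". It then continues: "Prior to hospital discharge patients will undergo a planned hemodynamic evaluation of the newly implanted rapid deployment bioprosthetic aortic valve", in order to confirm success. The Echocardiography section gives the same anchor: "The first one will be done during the index hospitalization, after AVR prior to discharge". Intervention description {11a} places randomisation and the start of study treatment together on the fifth postoperative day.

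On the time of allocation, Sequence generation {16a} has the participant receive a number and the "corresponding intervention upon confirmation at the first clinic visit".

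**The concern.** Eligibility should be fixed by what is known before allocation. Here one inclusion criterion has a window that closes at discharge, while allocation and first dose come on day 5. Between the two, a stroke, infarction, reoperation or valve thrombosis occurs on assigned treatment and also makes the operation unsuccessful as defined. The pre-discharge echocardiogram has the same problem if it is done after day 5, since early thrombus could affect the gradient.

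If anyone used that failure to drop a randomised patient, the exclusion would depend on an outcome that the assigned drug may cause or prevent, and the two arms could lose different kinds of patient. Staff and patients know the allocation, and the section on blinding accepts that staff may introduce bias when they complete case report forms. Once outcomes are known, the question can no longer be settled neutrally.

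**Working it through.** **1. Time anchors side by side**

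| Item | Time | Section |
|---|---|---|
| Randomisation and first dose | Postoperative day 5 | {11a}, {13} |
| Echocardiogram that confirms success | Before discharge, no link to randomisation | {10}, {13}, Echocardiography |
| Absence of complications | Whole hospital stay, to discharge | {10}, {13} |
| Safety composite | Randomisation to 3 months | Secondary outcome measures |
| Day of discharge | Not given | – |

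The eligibility window extends past randomisation for every patient discharged after day 5.

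**2. Overlap between disqualifying events and outcomes**

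- Stroke and myocardial infarction are components of the safety composite.
- Reoperation is an exploratory outcome. If done for bleeding, it would also reflect a VARC-3 bleeding event, which the composite counts.
- Clinically significant valve thrombosis is the overt form of the disease that the trial aims to prevent.

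**3. What the analysis rules say about such a patient**

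- {11b} and {20c} keep patients in their allocated arm for intention-to-treat. Neither mentions a randomised patient who later fails an inclusion criterion.
- {20a} tests the safety composite for non-inferiority per-protocol, so the intention-to-treat statement does not cover that test.
- {20c} defines per-protocol by receipt of assigned treatment and does not mention success.

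The article therefore neither orders nor forbids removal.

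**4. Time of allocation**

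The timeline has a visit at 6 weeks, outside the study protocol, and a protocol visit at 90 ± 5 days. No clinic visit falls on day 5, so assignment at a first clinic visit in {16a} conflicts with {11a} and {13}.

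**5. Scale**

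No stated figure depends on this rule. For context, the sample size reproduces. With 30% against 12% (a 60% reduction), two-sided 0.05, 80% power and mean proportion 0.21:

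n per arm = [1.96·√(2·0.21·0.79) + 0.8416·√(0.30·0.70 + 0.12·0.88)]² / 0.18² = (1.129 + 0.473)² / 0.0324 ≈ 79.2, rounded up to 80.

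That is 160 in total against the stated 158. Power at 79 per arm is 79.9%.

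The article gives no rate of failure after randomisation, so the following are assumptions.

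*Loss of precision.* Share of the 166 randomised who are removed, and power for the primary comparison:

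| Removed | No other loss | Planned 5% loss as well |
|---|---|---|
| 0% | 81.8% | 79.8% |
| 5% | 79.8% | 77.7% |
| 10% | 77.6% | 75.5% |
| 20% | 72.6% | 70.4% |

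*Shift in an arm's safety rate.* Removing one patient with an event from an arm of n patients with x events changes the rate by x/n − (x−1)/(n−1) = (n−x)/[n(n−1)]. With n = 166/2 = 83:

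- x = 4 (4.8%): 79/6,806 = 1.16 points
- x = 17 (20.5%): 66/6,806 = 0.97 points

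So each removed event moves that arm's rate by about one percentage point. The number of such events cannot be derived from the article.

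**The case against.** The strongest reply is that nothing in the article removes a randomised patient. {20c} applies intention-to-treat to all outcomes, and {11b} treats overt valve thrombosis and ischaemic stroke during the study as events to be managed, not as loss of eligibility. This stands. A reader might infer that the plan breaks intention-to-treat, but the text does not support that.

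A reader might also take the withdrawal reason "if the participant meets an exclusion criterion that precludes further participation" as the route to removal. It names exclusion criteria. Success is an inclusion criterion, and none of its components is in the exclusion list.

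Nor does the definition delete early bleeding generally from the apixaban arm. Only bleeding that leads to reoperation negates success, whereas the composite counts all VARC-3 types.

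It is tempting to say that about four removed events would use up the 5-point margin. No event rate supports four. The planned test also sets the upper 95% confidence bound, not the point difference, against the margin. With 83 per arm and equal rates of 5% to 20%, the interval half-width, 1.96·√[2p(1−p)/83], is already 6.6 to 12.2 points, so a point shift cannot be read directly against 5.

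The allocation conflict is also narrower than it may seem. Implementation {16c} says "Once a patient has been successfully screened, a binary code that is to be allocated to each participant will be generated", which fits day 5. Only {16a} conflicts.

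Finally, {16a} and {16c} suggest that eligibility is settled first, only sentence order in {13} puts the echocardiogram after randomisation, and the schematic and schedule figures are not available here. This lowers confidence about when the echocardiogram is done. It does not remove the written rule that complications count up to discharge.

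**Conclusion.** The concern holds as a badly fixed eligibility rule. As written, the window for success stays open after randomisation and first dose, and events inside it overlap with trial outcomes. This permits outcome-dependent exclusion without prescribing it. The intention-to-treat statements make it less likely in the primary analysis. The per-protocol safety non-inferiority test is the most exposed, because its analysis set is not tied to a clear rule for such patients.

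The conclusion assumes that some patients are still in hospital after day 5, as the order of steps in {13} implies. The size of the effect is unknown. The scale figures show only that each removed event would matter by about one point in an arm. The mismatch over a first clinic visit in {16a} is a separate, smaller inconsistency in wording.

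**What to change.** - Define success, for eligibility, by the echocardiographic findings and the absence of the listed complications up to randomisation.
- State that all randomised patients stay in the intention-to-treat set.
- State that events after randomisation, including those before discharge, count as outcomes and never determine eligibility or membership of any analysis set, per-protocol included.
- Reconcile Eligibility criteria {10}, Inclusion criteria, Participant timeline {13} and Echocardiography with the day-5 randomisation in Intervention description {11a}.
- Reconcile the first clinic visit in Sequence generation {16a} with day 5. Implementation {16c} can stay.

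No change to when treatment starts is proposed. The cost is amendment wording and completing the already planned echocardiogram before randomisation.

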**Fig. 3 Fig3:**
[figure not shown]
Standard Protocol Items: Recommendations for Interventional Trials schedule of enrolment, interventions, and assessments

**Fig. 4 Fig4:**
[figure not shown]
Consent form

After hospital discharge, monthly telephone interviews will be conducted to remind the patients of their planned visit and to get information on any complications or unexpected events that might have occurred in the meantime. They will be asked about any side effects, and the number of remaining tablets to determine treatment adherence. Participants’ clinic visit based on the study protocol will take place 90 ± 5 days from the time of randomization. They will be interviewed for clinical and adverse events once again. Side effects, adverse events, any unplanned hospital or emergency room visits, or any bleeding events will be noted. The number of remaining tablets will be counted to determine treatment adherence. A scheduled cardiac CT and heart ultrasound will be performed.

### Sample size {14}

According to previous studies tracking HALT of bioprosthetic heart valves, the rate has been estimated to be up to 39% [4, 7–9] among surgical valves. It has been estimated that there might be a 60–70% decrease in the incidence of HALT of bioprosthetic valves among patients receiving oral anticoagulants when compared to antiplatelet therapy [21]. If it is to be expected that HALT of the biological valve in the study will occur in about 30% of control patients, a premise of a 60% decrease in the prevalence after a 3-month treatment period seems reasonable and relevant. The null hypothesis is that compared to the ASA controls, apixaban treatment will not mitigate HALT prevalence among patients after rapid deployment AVR following a 3-month treatment period. With 158 participants randomized 1:1, we expect to have 80% power (type I error < 0.2) to detect a significant difference (type I error < 0.05) between the study groups, thus rejecting the null hypothesis. To account for protocol violation, loss to follow-up, and withdrawal of consent in 5% of participants, we aim to randomize at least 166 patients.

### Recruitment {15}

The accrual rate is expected to be up to 7 participants per month with the recruitment period spanning over 24 months. We predict the need to screen about 200 individuals to meet the goal of enrolling 166 study participants. Recruitment sources include the Department of Cardiac Surgery University Hospital Center Zagreb. All potential participants will be logged in a password protected database on a secured, shared server, which will contain their contact information, date of contact, eligibility, recruitment source, and date of scheduled visit; identifiable health information will not be stored during recruitment.

## Assignment of interventions: allocation

### Sequence generation {16a}

We will use the R software to generate a random sequential list of binary codes by participant number. Blocks of fixed length will be applied to keep the number of both arms relatively balanced. Set seed function will be used to ensure that the randomization schedule is reproducible. Participants who have been screened and meet criteria will enter the randomization section and be assigned with the appropriate number and corresponding intervention upon confirmation at the first clinic visit.

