### Trial design {8}

This study is designed as a prospective, randomized, open-label, blinded endpoint, single-site superiority trial with two parallel groups. Patients will be randomized with a 1:1 allocation ratio. The trial is investigator initiated; it is planned, funded, and conducted without industry involvement.

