### Concealment mechanism {16b}

Only the (PI) will know what code corresponds to which treatment arm. Trial randomization codes will be kept on a password-protected Excel sheet located on a secure server to which only the PI will have access to.

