## Oversight and monitoring

### Composition of the coordinating center and trial steering committee {5d}

The overall responsibility for the study and its management will be with the PI. The trial steering committee is comprised of senior members of the Department of Cardiac Surgery at the University Hospital Center Zagreb. The steering committee will be responsible for the day-to-day running of the trial.

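### Fixed-length blocks in an open-label, single-site trial leave some allocations foreseeable, and the list is held by a PI not described as independent of recruitment

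*Protocol article*

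**What the plan says.** - **Design.** Trial design {8} describes a "prospective, randomized, open-label, blinded endpoint, single-site superiority trial with two parallel groups" and adds: "Patients will be randomized with a 1:1 allocation ratio". The article mentions no stratification.
- **Sequence.** Sequence generation {16a} has R "generate a random sequential list of binary codes by participant number", and then: "Blocks of fixed length will be applied to keep the number of both arms relatively balanced". A seed is set so that the list can be reproduced. The block length is not given.
- **Custody.** Concealment mechanism {16b}: "Only the (PI) will know what code corresponds to which treatment arm", and "Trial randomization codes will be kept on a password-protected Excel sheet located on a secure server to which only the PI will have access to".
- **Roles.** Section {5d}: "The overall responsibility for the study and its management will be with the PI". The same section leaves the daily conduct of the trial to the steering committee. Implementation {16c} gives enrolment to trained research assistants.
- **Time of assignment.** Intervention description {11a} puts randomization on postoperative day 5. Section {16a} ties assignment to confirmation at the first clinic visit. Section {16c} ties it to successful screening, which Eligibility criteria {10} places before surgery.

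**The concern.** Section {16b} protects concealment by keeping secret which binary code stands for which arm. In an open-label trial that secret does not last, because the first patient whose code and drug are both seen gives it away. From then on, concealment from site staff depends on the sequence being unpredictable, and a constant block length weakens that in a single list at a single department.

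Separately, the one person who can see every future assignment also manages the trial.

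At stake is selection at entry. If someone who foresees the next arm can influence whether or when a patient is randomized, the arms may differ at baseline. Blinded CT reading and blinded adjudication (Who will be blinded {17a}) protect how outcomes are assessed. They do not protect who enters which arm, and an intention-to-treat analysis cannot repair it.

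**Working it through.** **Plan's own figure.** The article states no figure for predictability, so there is none to reproduce. The only number taken from it is the 166 to be randomized (Sample size {14}). That agrees with 158 evaluable and 5% loss: 158 × 1.05 = 165.9.

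**Inputs.** 1:1 allocation, one sequence, fixed block length 2b. The length is assumed to be 4, 6 or 8.

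**Step 1: assignments certain in advance.** Within a block, an assignment is forced once one arm is used up. The expected number of A's that follow the last B is b/(b+1), and likewise for B's after the last A. The expected number forced per block is therefore 2b/(b+1). Dividing by 2b gives a share of 1/(b+1).

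**Step 2: best guess.** A guesser who knows the length always names the arm with more places left. For length 4 the success probabilities at the four positions are 1/2, 2/3, 2/3 and 1. Their sum is 2.833, and 2.833/4 = 0.708. Lengths 6 and 8 come from the same recursion.

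| Block length | Certain share | Of 166 | Best guess correct |
|---|---|---|---|
| 4 | 1/3 = 33% | 55 | 71% |
| 6 | 1/4 = 25% | 42 | 68% |
| 8 | 1/5 = 20% | 33 | 67% |

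Simple randomization gives 0% certain and 50% guessed correctly.

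**Step 3: varied lengths.** This was simulated with 800 trials of 166 patients and a guesser who knows the set of lengths but not the current one. As a check, fixed length 4 in the same simulation returned 32.9% and 70.9%, against the exact 33.3% and 70.8%.

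| Lengths | Certain share | Best guess correct |
|---|---|---|
| 4, 6 | 5.6% | 69% |
| 2, 4, 6 | 4.2% | 70% |
| 4, 6, 8 | 2.2% | 68% |

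Varying the lengths nearly removes certainty but hardly changes guessing. It does nothing about a person who holds list and key, who knows every assignment under any block scheme.

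**Step 4: room to act on foresight.** Four kinds of eligibility item can be settled, or can change, after surgery:
- Successful valve replacement is defined mostly by echocardiographic limits and named complications (section {10}), so it leaves little discretion.
- Postoperative atrial fibrillation has a stated duration limit, so it also leaves little.
- Ability to start the study drug in the window and contraindications to either drug class (Exclusion criteria) do leave discretion.

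Recruitment {15} expects about 200 screened for 166 enrolled, so 200 − 166 = 34 are lost for all reasons together.

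**Step 5: assignment times.** If a code is allocated at preoperative screening, as {16c} together with {10} can be read, it exists before the postoperative items are decided. If it is allocated on day 5 or at a clinic visit, it need not. The three statements cannot all describe the same event.

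**The case against.** The strongest reply is that list-holder and enrollers are already separated. Only the PI has the list, research assistants enrol, and no section gives the PI a part in enrolment or in judging eligibility. This stands. A reader might infer that upcoming allocations are simply known to the people who recruit, but the article does not support that. Full knowledge is documented for one person with no stated enrolment role. Everyone else must infer an undisclosed block length and keep count. What remains is that the PI manages the trial and is not described as independent of recruitment.

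Other points on that side also hold:
- Withholding the block length is normal practice and is not criticised here. A reader might quote 50% certain (83 of 166), but that needs blocks of 2, which nothing in the article suggests.
- Eligibility is largely numeric, and randomization is set for a named day, so the room for selection is limited.
- Section {16a} already requires criteria to be met and confirmed before assignment. The principle is therefore present, but the times attached to it conflict.
- An effect on HALT is not shown. A predictable share is not an estimate of bias, and the article identifies no day-5 characteristic by which staff could select on HALT risk. Selection on bleeding risk is easier to imagine, and bleeding belongs to the secondary outcome.

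**Conclusion.** The point holds in a limited form. Fixed blocks in an open-label, apparently unstratified, single-site sequence let an attentive member of staff foresee part of it. With lengths of 4 to 8, 20% to 33% is certain (33 to 55 of 166), and the best guess is right 67% to 71% of the time. These figures assume that the length is in that range, that it has been inferred, and that past assignments are tracked. Custody by the PI is a separate weakness, which changing the block scheme would not touch.

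Selection at entry is possible because some late eligibility items leave discretion. Neither its occurrence nor its size can be derived from the article. A reader might infer that the primary comparison is biased, but the text supports only that an avoidable route to bias is open. The point merits a change and does not undermine the design as a whole.

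**What to change.** For patients still to be randomized:
1. Move the list, the key, and the script with its seed (which can regenerate the list) to a custodian who neither recruits nor analyses. The independent trial statistician named in section {21a} is not suitable, because that person performs the analyses and section {17a} keeps associated personnel blinded until the data have been analysed.
2. Release each assignment singly, and only after final postoperative eligibility has been logged with date and time. Steps 1 and 2 are the main remedy.
3. Generate the remaining list with randomly varying block lengths not disclosed to site staff.
4. Reconcile the assignment times in {11a}, {16a} and {16c}, and state which eligibility items must be complete at release.

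The cost is a new script, a new file owner, a documented mid-trial change of list, and an arm imbalance of a few patients. Step 3 alone is a partial cure, since guessing stays near 68% to 70%.

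Trial status expects recruitment to be complete by the end of 2025. If it is already complete, the final report should give the block length, who had access to the list, and the reasons for non-randomization. It should also check whether baseline risk tracks the allocation that could have been predicted.
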